### Data collection, cleaning and storage

Across the study area, incentivised volunteers report pregnancies to monitors, each responsible for a population of around 4000. A monitor visits every pregnant woman identified, ascertains the estimated month of pregnancy, offers information about the study and invites her to join. If consent is given, the monitor measure the woman’s height and MUAC, and administers a first questionnaire. All children born to pregnant women recruited between 1st October 2013 and 10th February 2015 will be followed up within 72 hours of birth, and at 3, 6, 9, 12 and 18 months. Trained growth monitors conduct measurements at birth, and then visit the mother and child at 3, 6, 9, 12 and 18 months to measure length (using a Shorr board), weight (using a Seca 384 scale), MUAC, and administer a structured questionnaire. All monitors’ measurements were validated twice against a gold standard, and we calculated intra-observer and inter-observer technical error of measurement for length and other anthropometric outcomes.

We use mobile phones programmed using the CommCare platform for data collection. The monitoring team checks the number of interviews completed and type of data collected every week in order to promptly identify and address possible problems. The data are downloaded every two weeks and checked for errors using automated do files and manual inspections. Names of participants are collected but removed before data storage. Final datasets contain numerical identifiers for cluster individual participants. The data are stored and backed up every two weeks on a server.

### Blinding

Due to the nature of the intervention, the participants and intervention teams are not blinded to the allocation of clusters. While members of the monitoring team are not given information about the allocation of individual clusters during their training, they are likely to see some of the intervention workers (SPKs) and hear about them in the course of their monitoring activities, which makes complete blinding difficult. To minimise this effect, the intervention and monitoring teams meet on different days and do not discuss individual cases of mothers and children. The trial statistician will conduct interim and final analyses blind to allocation.

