##### Recruitment, supervision and training of intervention workers

In the intervention arm, we recruited 60 SPKs through consultation with local Village Health Sanitation and Nutrition Committees (VHSNCs) and *Anganwadi Sevikas*. The SPK’s working area is her own village and its attached hamlets. She is paid a monthly stipend equivalent to that of existing *Anganwadi Sevikas.*

Six supervisors recruited by the study team support 10 SPKs each. SPKs and their supervisors receive phased trainings and attend bi-monthly supervision meetings. For home visits, training sessions covered knowledge and skills for counselling to improve Infant and Young Child Feeding practices, care-seeking for common childhood illnesses, and household-based strategies to prevent illness including handwashing, safe handling of water and food, and disposal of faeces. The training preparing SPKs for participatory group meetings included practical sessions on conducting women’s group meetings using a participatory learning and action approach, as well as interacting with existing community health workers.

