### Analysis plans

#### Interim analysis

We do not expect any adverse effects of the intervention but plan to carry out two interim analyses in 2014 and 2015, which will be reported to an independent DMC convened according to the DAMOCLES charter [45]. At these meetings, the DMC will examine data for the following:Recruitment and retention (i.e. the number of births registered in the study and followed up);Mean length for age z score and weight for height z scores at the most recent measurement for each childTwo measures of intervention coverage: % of mothers visited by an SPK in the last three months; % of mothers who attended a women’s group meeting in the last three months;Two measures of monitoring quality: mean difference in days between expected and actual interview dates; average difference between first and second length measurement for most recent measurement).

The DMC members will look at these data by allocation arm independently, write down their immediate assessment, and then contribute to a general discussion with the research team. At the first interim analysis in 2014, the DMC observed a shortfall in the number of live births compared to what was expected in the sample size calculation. The DMC recommended extending the recruitment period until we reached the target sample size. This was achieved in February 2015.

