#### Final analysis

Final analyses will be by intention-to-treat and include all mothers who were pregnant and had a live birth during the recruitment period (1st October 2013 – 10th February 2015) and their infants, regardless of whether they received the intervention or not. We will test for differences between intervention and control areas in the main outcomes of interest using linear regression for continuous outcomes and logistic regression for binary outcomes, adjusting for clustering using random effect models. We will examine levels of missing data for the primary and secondary outcomes, and plan to use multiple imputation if these exceed 10%.

For the final DMC, we plan to carry out three sub-group analyses. The first will examine differences in children’s LAZ at 18 months according to the intensity of their mothers’ exposure to group meetings (number of meetings attended), adjusting for maternal education, multi-dimensional poverty status, and tribal status. The second sub-group analysis will examine differences in growth outcomes between arms by wealth quintile to understand the equity impact of the intervention. The third sub-group analysis will examine differences in growth outcomes for boys and girls. The final analysis will be presented according to the CONSORT requirements for cluster randomised controlled trials [46,47]. Both the interim and final analyses will be conducted by the trial statistician ([name]).

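### The statistician is described as blind, but the interim data reviewed by arm include visits by a worker who exists in only one arm

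*Protocol article*

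**What the plan says.** Under Blinding, the protocol article states: "The trial statistician will conduct interim and final analyses blind to allocation". The Final analysis section confirms that one person does both: "Both the interim and final analyses will be conducted by the trial statistician". No separate unblinded statistician is named.

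The Interim analysis section announces a "plan to carry out two interim analyses in 2014 and 2015" and reports that the first has taken place. The material for the DMC includes mean length-for-age (LAZ) and weight-for-height Z scores at each child's latest measurement, and two coverage measures: the percentage "of mothers visited by an SPK in the last three months; % of mothers who attended a women’s group meeting in the last three months". On procedure, it has each DMC member view the results split by arm alone, record a first opinion, "and then contribute to a general discussion with the research team".

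On who delivers the intervention, the section on recruitment of workers says: "In the intervention arm, we recruited 60 SPKs". According to the Abstract, control clusters get only the support to village committees.

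**The concern.** Coding the arms A and B blinds an analyst only if nothing tabulated by code defines an arm. A visit from an SPK is itself part of the intervention. Whoever tabulates SPK visits by arm therefore sees which code is the intervention arm, with mean LAZ for the same codes in the same interim package.

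What is at stake is mainly whether a stated safeguard is true. Readers of the final report would credit the trial with a blind statistician, although the procedure described very probably removed that blindness in 2014. Recruitment began on 1 October 2013, so no enrolled child could reach 18 months before about April 2015. The arms could thus have been known before any primary outcome measurement existed.

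A second, lesser matter is that the DMC moves straight from by-arm review to a discussion with the research team, and the article states no limit on what may be shared.

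**Working it through.** The protocol gives no figure on this point to reproduce. The check sets the sections side by side and adds one illustration.

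**Step 1: who sees what.** The statistician conducts the interim analyses (Final analysis). The interim data include SPK visits and are viewed by arm (Interim analysis). The tables must therefore be split by arm, at least under codes, and the article names nobody else as producing them.

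**Step 2: can the SPK variable be non-zero in both arms?** SPKs were recruited for the intervention arm, and each works in her own village and its hamlets (Recruitment, supervision and training). Clusters are separated by rivers, hills or distance (Cluster size and selection). Control clusters receive committee support only (Abstract). Control-arm SPK coverage should be close to nil. If it is exactly nil, one reported visit under a code identifies that code.

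**Step 3: illustration allowing some misreporting or spill-over.** Let c be control coverage, t intervention coverage, n mothers per arm and D the design effect. Under a normal approximation, the probability that the arm with the higher observed coverage is the intervention arm is

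P = Φ[(t − c) / √{(c(1 − c) + t(1 − t)) / (n/D)}].

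The document gives neither coverage nor interim numbers, so these are assumptions: n of 300 or 600, and D of 1.84 or 10. The lower D is the sample size formula, 1 + 24 × 0.035 = 1.84. The higher D allows for coverage that varies strongly by village because each village has one worker.

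Worked case: c = 0.05, t = 0.20, n = 300, D = 10. Then n/D = 30, the standard error is √(0.2075/30) = 0.083, z = 0.15/0.083 = 1.80, and P = 0.96.

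| Control c | Intervention t | P over the four n, D combinations |
|---|---|---|
| 0% or 5% | 50% | 1.00 throughout |
| 5% | 20% | 0.96 to 1.00 |
| 5% | 10% | 0.77 to 0.99 |

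Only very poor delivery leaves real doubt about which arm is which.

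**Step 4: the final stage.** The Final analysis section plans an analysis of LAZ by number of group meetings attended. Exposure data therefore return to the same analyst, and nothing in the article says this happens after the primary result is fixed.

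**Step 5: the DMC procedure.** The sequence is by-arm review, written individual assessment, "and then contribute to a general discussion with the research team". The text gives the order of events but not what is disclosed in that discussion.

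**The case against.** The other side has several good points, and they narrow the conclusion.

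- **Disclosure to the research team.** A reader might infer that the DMC shows by-arm LAZ to the team. The article does not say so. Members look at the data independently. The one outcome reported, a shortfall in live births and longer recruitment, needs no by-arm data. The DMC is also convened under a charter that is not shown and may set session rules. What stands is that the wording does not exclude disclosure.
- **Open analytic choices.** A reader might infer that an unblinded statistician was free to choose the model, the subgroups and the handling of missing data. The Final analysis section already fixes intention-to-treat, linear and logistic regression with random effects, three named subgroup analyses, and a 10% threshold for multiple imputation that does not depend on knowing the arms. Further detail may stand in an analysis plan not shown.
- **Unblinded measurement.** A reader might call the length measurement unblinded. The Blinding section describes partial shielding: monitors are not told cluster allocation in training, and the two teams meet on different days and do not discuss individual cases. It openly admits that complete blinding is difficult.
- **Group attendance.** A reader might assume attendance is nil in control clusters, since the ethics section says no group meetings are otherwise available. The lead organisation has used participatory approaches in these districts since 2004, and the article mentions women's groups from previous interventions, so some control attendance is possible. This item reveals the arm less certainly than SPK visits do.

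It can also be said that a DMC normally sees data by arm. That is right, and it is no part of the criticism.

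**Conclusion.** The concern holds in a limited form. The statement that the statistician works blind is not compatible with the same person producing by-arm interim data that contain SPK visits. Identification of the intervention arm from the 2014 interim onward is very probable: practically certain at 50% coverage against 0–5%, and at least 0.96 at 20% against 5%, under the assumptions shown. It rests on reading the article as it stands, with the statistician tabulating the coverage measures. If someone else did so and the statistician never saw them by code, the claim could be true, but the article would need to say so.

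On the DMC, the supported conclusion is only that the wording leaves open whether by-arm LAZ can reach the research team. No actual bias is shown, and sample size, power and alpha are unaffected. This is a correction to a stated safeguard that should be made, not evidence that the results are compromised.

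**What to change.** 1. **Remaining interim and final analysis.** Re-code the arms, and keep SPK-visit and meeting-attendance variables out of the statistician's coded outcome dataset until the primary LAZ analysis is run and locked. The stored datasets carry cluster and participant identifiers, so these need new numbers in the extract too; otherwise the old codes can be matched back. Existing data staff with no part in length measurement should tabulate coverage for the DMC. The monitoring team should not do it, because by-arm coverage would reveal allocation to those who measure length. If no such staff exist, an independent person is needed.
2. **Blinding section.** State that the statistician was not effectively blind at the 2014 interim, which cannot be undone. If item 1 is not adopted, withdraw the claim altogether.
3. **Interim analysis section.** State that by-arm data are discussed among DMC members only, and that the research team receives recruitment and data-quality information and the recommendation. If the charter already says this, a sentence referring to it is enough.

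The cost is wording, a changed extract and a changed agenda. The downsides are that the DMC works from separate coverage and outcome files, and that the blinding reported becomes less favourable.

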### Study outcomes

The primary outcome of the trial is children’s length-for-age Z scores of 2006 WHO Growth Standards at 18 months. Secondary outcomes are described in Additional file 1, along with details of their inclusion in the interim Data Monitoring Committee (DMC).

### Analysis plans

#### Interim analysis

We do not expect any adverse effects of the intervention but plan to carry out two interim analyses in 2014 and 2015, which will be reported to an independent DMC convened according to the DAMOCLES charter [45]. At these meetings, the DMC will examine data for the following:Recruitment and retention (i.e. the number of births registered in the study and followed up);Mean length for age z score and weight for height z scores at the most recent measurement for each childTwo measures of intervention coverage: % of mothers visited by an SPK in the last three months; % of mothers who attended a women’s group meeting in the last three months;Two measures of monitoring quality: mean difference in days between expected and actual interview dates; average difference between first and second length measurement for most recent measurement).

The DMC members will look at these data by allocation arm independently, write down their immediate assessment, and then contribute to a general discussion with the research team. At the first interim analysis in 2014, the DMC observed a shortfall in the number of live births compared to what was expected in the sample size calculation. The DMC recommended extending the recruitment period until we reached the target sample size. This was achieved in February 2015.

#### Final analysis

Final analyses will be by intention-to-treat and include all mothers who were pregnant and had a live birth during the recruitment period (1st October 2013 – 10th February 2015) and their infants, regardless of whether they received the intervention or not. We will test for differences between intervention and control areas in the main outcomes of interest using linear regression for continuous outcomes and logistic regression for binary outcomes, adjusting for clustering using random effect models. We will examine levels of missing data for the primary and secondary outcomes, and plan to use multiple imputation if these exceed 10%.

For the final DMC, we plan to carry out three sub-group analyses. The first will examine differences in children’s LAZ at 18 months according to the intensity of their mothers’ exposure to group meetings (number of meetings attended), adjusting for maternal education, multi-dimensional poverty status, and tribal status. The second sub-group analysis will examine differences in growth outcomes between arms by wealth quintile to understand the equity impact of the intervention. The third sub-group analysis will examine differences in growth outcomes for boys and girls. The final analysis will be presented according to the CONSORT requirements for cluster randomised controlled trials [46,47]. Both the interim and final analyses will be conducted by the trial statistician ([name]).

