### Trial participants

Participants are women in the third trimester of pregnancy residing in the study clusters and identified between the 1st of October 2013 and 31st December 2015. Incentivised volunteers report every newly identified pregnancy to a member of the monitoring team. A study monitor then approaches the pregnant woman to explain the study and seek her consent for participation. Every pregnant woman residing in the study clusters and identified between the 1st October 2013 and 10th February 2015 is also asked for permission to follow-up her liveborn child for a period of 18 months. Pregnant women will be enrolled until the 31st December 2015 in order to measure the impact of the interventions on maternal nutrition in pregnancy.

We exclude stillbirths and neonatal deaths, infants whose mothers have died, infants with congenital abnormalities, multiple births, and mother/infant pairs who migrate out of the study area permanently during the study period. We define permanent migration as mother/infant pair missing more than two consecutive interviews (i.e. being absent from the study area for at least six months) at any point during the infant’s 18 months follow-up period.

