#### Secondary research questions

Does the strategy lead to improvements in feeding, infection control and caring practices for children 0–18 months?Does the strategy lead to increases in food intake and dietary diversity for women during pregnancy and lactation?What operational factors affect the strategy’s delivery and impact?What are the potential scalability, operational requirements, cost and impact of the strategy beyond the trial area?

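### The final analysis set is dated by live birth but the followed child cohort by the mother's recruitment, so read literally, children born after 10 February 2015 are followed to 18 months and then left out

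*Protocol article*

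**What the plan says.** Three sections of the protocol article use the same pair of dates.

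- **Trial participants** dates the child cohort by the mother. Every pregnant woman "identified between the 1st October 2013 and 10th February 2015 is also asked for permission to follow-up her liveborn child", for 18 months. Entry is late in pregnancy: "Participants are women in the third trimester of pregnancy residing in the study clusters".
- **Data collection, cleaning and storage** does the same: "All children born to pregnant women recruited between 1st October 2013 and 10th February 2015 will be followed up within 72 hours of birth", and then at 3, 6, 9, 12 and 18 months.
- **Final analysis** attaches the dates to the birth. The intention-to-treat analyses will "include all mothers who were pregnant and had a live birth during the recruitment period"; the sentence goes on "during the recruitment period (1st October 2013 – 10th February 2015) and their infants".

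Trial participants also keeps enrolment of women open beyond the child cut-off: "Pregnant women will be enrolled until the 31st December 2015 in order to measure the impact of the interventions on maternal nutrition in pregnancy". This serves one of the secondary research questions: "Does the strategy lead to increases in food intake and dietary diversity for women during pregnancy and lactation".

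**The concern.** One date range cannot bound both the recruitment of women in the third trimester and the births of their children. A woman recruited in January or early February 2015 will often deliver after 10 February. Her child belongs to the followed cohort under two sections and lies outside the analysis set under the third.

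Two things are at stake. The first is precision for the primary outcome, length-for-age Z score (LAZ) at 18 months, because children who have been fully measured would be discarded. The second is that the text allows two primary analysis populations, and the choice between them should not remain open once outcomes are known. CONSORT reporting, which the article commits to, needs one denominator.

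A smaller consequence sits in the same sentence. It speaks of the final analyses in general and is not limited to child outcomes. Taken literally it also shuts out women enrolled after 10 February 2015, whose enrolled pregnancy cannot have ended in a live birth by that date.

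**Working it through.** **Inputs.** From Sample size: difference 0.15 LAZ, SD 1, 80% power, alpha 0.05 (taken as two-sided), ICC 0.035, design effect D = 1.8, 2772 children before and 2520 after attrition, 120 clusters enrolled. From Trial participants and Final analysis: the dates. From Trial timeline and status: trial end on 31 January 2017. Assumed, because the article does not give it: the mean lag from recruitment to birth.

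**1. The plan's own figure.** n per arm = 2 × (1.96 + 0.84)² / 0.15² = 698, or 1396 in total. Multiplied by 1.8 this is 2513, which reproduces 2520. With 2520 children (1260 per arm), power = Φ(0.15 / √(2 × 1.8 / 1260) − 1.96) = 80.1%. The sample size is not in dispute.

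**2. Window.** 1 October 2013 to 10 February 2015 is 498 days, or 498 / 30.44 = 16.4 months.

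**3. Can the late-born children be measured in time?** A woman recruited in the third trimester on 10 February 2015 delivers by about mid-May 2015. Her child reaches 18 months by about mid-November 2016, before the trial ends. Trial length gives no reason to leave these children out.

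**4. Share affected.** With steady accrual, the share of the followed cohort born after the cut-off is mean lag / 16.4. Nothing offsets this at the start, because recruitment itself begins on 1 October 2013. A lag of 1 month gives 6.1%, 2 months 12.2%, 2.8 months 17.1%, and 3 months (the upper limit) 18.3%.

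**5. Power.** The share is applied to 2520, the analysed number. (Taking 10% off 2772 gives 2495, because the plan's 2772 is 2520 × 1.1; applying the share to 2520 avoids mixing the two conventions.) The last column uses D = 1 + (m − 1) × 0.035, with m the number of analysed children divided by 120.

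| Mean lag (assumed) | Children lost of 2520 | Left | Power, D = 1.8 | Power, D by cluster size, 120 clusters |
|---|---|---|---|---|
| none lost | 0 | 2520 | 80.1% | 82.3% |
| 1 month | 154 | 2366 | 77.6% | 80.9% |
| 2 months | 308 | 2212 | 74.8% | 79.4% |
| 3 months | 462 | 2058 | 71.8% | 77.6% |

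In the last column D is 1 + 20 × 0.035 = 1.70 with nobody lost (m = 21). It falls as m falls, so the loss of power is smaller.

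**The case against.** The strongest reply is that the sentence is loose drafting. If the birth date alone defined the set, saying that the mothers were pregnant would add nothing. The phrase can be read as pregnant, and so recruited, in the window, with a live birth to follow. The window is called the recruitment period, and two other sections say plainly that all children of women recruited in it are followed. This is a fair reading and may be what was meant. It does not remove the need to reword, since the literal text says otherwise and nothing elsewhere in the article overrides it.

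Three stronger inferences are tempting, and the article does not support them.

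- *That the analysed sample must fall below target.* Interim analysis reports a shortfall in live births and then an extension of recruitment until the target was reached in February 2015. It does not say whether that target counted births or recruited women. If births, those up to 10 February already meet it and the later children are extra. Excluding them then wastes precision but does not break the plan. If recruited women, there is a real shortfall.
- *That the arms are biased.* The calendar cut-off is the same in both arms. A bias would need the timing of recruitment in pregnancy to differ by arm, and nothing shows that it does.
- *That the maternal nutrition question has lost its later sample.* Trial participants states the purpose of enrolling to 31 December 2015, and a separate analysis set for a secondary maternal outcome is something a condensed article may leave to the full plan. What remains is that the sentence, as worded, is not confined to child outcomes.

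**Conclusion.** The inconsistency stands. Two sections define the child cohort by the mother's recruitment date, and Final analysis applies the same dates to the live birth. On the literal reading, children born after 10 February 2015, up to about mid-May 2015, are followed to 18 months and excluded from the primary analysis.

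The size depends on an assumed lag and on steady accrual: about 6–17% of the followed cohort for mean lags of 1 to 2.8 months. The cost in power is about 2.5 points for a 1-month lag and 5.3 points for 2 months at D = 1.8 (80.1 − 77.6; 80.1 − 74.8). It is about 1.4 and 2.9 points if the design effect shrinks with cluster size over 120 clusters (82.3 − 80.9; 82.3 − 79.4). The loss is modest, but it would buy nothing and is easily avoided. The exclusion may be unintended. The documents support neither a certain shortfall against target nor a bias between arms.

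**What to change.** Reword the opening sentence of Final analysis so that:

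- the child analyses include all eligible live-born infants of women recruited between 1 October 2013 and 10 February 2015, whatever the date of birth, analysed by cluster as randomised;
- the set is expressly limited to child outcomes, so that it does not literally exclude the women enrolled to 31 December 2015 for maternal nutrition.

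Use one term for the mother's entry date, since Trial participants speaks of identification and Data collection of recruitment.

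The cost is one sentence in the protocol and analysis plan. The children are already due to be followed, so no data collection, sample size or timeline changes. The change should be recorded before the final data are analysed by arm.

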### Randomisation

The randomisation, which took place in July 2013, was stratified by district and by number of hamlets per unit (see Figure 2: Trial design). In each district, Ekjut invited village leaders, teachers, frontline workers such as *Anganwadi Sevikas* and ASHAs, members of local governance bodies (Panchayati Raj Institutions), and Women and Child Development functionaries to participate in a meeting. Members of the research team explained the purpose of the study and the randomisation process. A list of numbered clusters was placed on a wall. The list was stratified into three groups: clusters with no hamlets, clusters with one to two hamlets, and clusters with three or more hamlets. Meeting participants placed a set of numbered balls corresponding to the clusters in each stratum in a local ‘tombola’ (lottery device), and sequentially allocated each ball/cluster to the intervention or control arms.

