### Sample size

The primary outcome of the study is mean length for age Z (LAZ) score at 18 months. In a meta-analysis of complementary feeding trials testing interventions to improve growth, nutrition education interventions had a mean effect size of 0.2 Z scores on LAZ at 18 months (range 0.04, 0.64) [38]. We therefore chose 0.15 as a conservative estimate of the effect size. The intra-cluster correlation (ICC) for stunting was estimated at 0.035 using an analysis of 42 DHS studies and our own data from the study areas [43]. The unit of randomisation (cluster) is a village and its attached hamlets. We expect around 25 live births per year in each cluster. Accounting for 10% attrition due to loss to follow-up and mortality, recruiting all eligible children born over 12 months in 110 clusters (2772 children before and 2520 after attrition), will allow us to detect a difference of 0.15 in mean LAZ scores between intervention and control arms (SD of 1) with 80% power and alpha of 0.05, and a design effect (D) of 1.8, calculated as D = 1 + (25–1) x 0.035. This sample size also gives the trial 80% power to detect a 13% reduction in the prevalence of stunting (from 60% to 52.5%), a 19% reduction in the prevalence of wasting (from 40% to 32.5%), and a reduction in the infant mortality rate greater than 45% (from 100 to 55 per 1000 livebirths) [44]. To account for the possibility of clusters dropping out of the study and for attrition rates exceeding our 10% estimate, we enrolled a total of 120 clusters (villages).

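### The stated final model omits the district and hamlet strata used to randomise; if these predict LAZ, its standard errors are too large and its test conservative

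*Protocol article*

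**What the plan says.** The Randomisation section says that allocation "was stratified by district and by number of hamlets per unit". In each of the two districts the cluster list was split into "clusters with no hamlets, clusters with one to two hamlets, and clusters with three or more hamlets", which makes six strata (2 x 3).

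The Final analysis section gives one model statement for all main outcomes: linear regression for continuous and logistic regression for binary outcomes, "adjusting for clustering using random effect models". It names neither district nor hamlet group. The same section does list covariates for the sub-group analysis of exposure to group meetings, which is done "adjusting for maternal education, multi-dimensional poverty status, and tribal status". Those covariates are not attached to the comparison between arms.

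Under Data collection, cleaning and storage, the article says that once a woman consents, "the monitor measure the woman’s height and MUAC". Maternal height appears in no analysis that the article describes.

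The Sample size section plans for a difference of 0.15 in mean LAZ with an SD of 1, "with 80% power and alpha of 0.05" and an ICC of 0.035.

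**The concern.** Stratified randomisation balances the arms on the strata, so differences between strata in mean LAZ do not contribute to the sampling error of the arm comparison. A model with only a random cluster intercept does not know this. It counts the between-strata differences as part of the cluster variance and reports a standard error that includes them. The result is intervals that are too wide, a test whose true size is below 5%, and some lost power.

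District and number of hamlets were presumably chosen as strata because they might matter for child growth, so the possibility is not remote. The target difference is small and planned power is 80%, so a few points are worth having when the data are already in hand.

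Maternal height is a separate and lesser matter. It played no part in the randomisation, so leaving it out does not miscalibrate the test. It is a plausible predictor of child length that the intervention cannot change, and using it could add precision.

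**Working it through.** **Reproducing the planned size.** Two means, difference 0.15, SD 1, two-sided alpha 0.05 (sidedness assumed), power 80%: 2 x (1.960 + 0.842)² / 0.15² = 697.7, so 698 per arm and 1396 in total. Multiplying by the stated design effect of 1.8 gives 2513; by the unrounded 1 + 24 x 0.035 = 1.84 it gives 2569. Both are within 3% of the stated 2520. Power at 2520 is 80.1% or 79.3%. The planned size therefore rests on no covariate adjustment.

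**Setting for the check.** 120 clusters as enrolled, 2520 / 120 = 21 children each, total variance 1, ICC 0.035. The between-cluster variance is 0.035. The within-cluster contribution to a cluster mean is 0.965 / 21 = 0.04595.

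**Standard error that the stated model reports.** SE0 = sqrt(4 x (0.035 + 0.04595) / 120) = 0.0519.

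**True standard error under stratified randomisation.** If the strata explain a share R of between-cluster variance, SE1 = sqrt(4 x (0.035(1 - R) + 0.04595) / 120). A model with stratum terms reports SE1; the stated model reports SE0. The article gives no value for R, so 0-30% is an assumed range.

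- True alpha, strata omitted: 2 x [1 - Φ(1.96 x SE0/SE1)]
- Power, strata omitted: Φ((0.15 - 1.96 x SE0)/SE1)
- Power, strata included: Φ(0.15/SE1 - 1.96)

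| R (assumed) | SE1 | SE0/SE1 | True alpha, omitted | Power, omitted | Power, included |
|---|---|---|---|---|---|
| 0 | 0.0519 | 1.000 | 0.050 | 82.3% | 82.3% |
| 10% | 0.0508 | 1.022 | 0.045 | 82.9% | 83.9% |
| 20% | 0.0496 | 1.046 | 0.040 | 83.4% | 85.6% |
| 30% | 0.0485 | 1.072 | 0.036 | 84.0% | 87.2% |

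The reported interval is 2-7% wider than it needs to be for R of 10-30%. The fair comparison is along each row, because stratified randomisation lowers the true variance whether or not the model uses the strata. The gain from stratum terms is thus about 1, 2 or 3 points. Comparing the last column with 82.3% throughout would overstate it.

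**Maternal height.** Suppose it explains 8% of within-cluster variance (an assumption). The within-cluster contribution falls to 0.92 x 0.04595 = 0.04228.

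- With R = 0: SE = sqrt(4 x (0.035 + 0.04228) / 120) = 0.0508 and power 84.0%, against 82.3%.
- On top of strata at R = 10%, 20% or 30%: power 85.7%, 87.3% or 88.9%, against 83.9%, 85.6% or 87.2%.

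That is just under 2 points in each case.

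**The case against.** The strongest reply is that this is silence, not a decision. The article condenses a fuller plan, and covariate lists commonly sit in an analysis plan that is not shown. Nowhere does it say that the model is unadjusted or that the strata are excluded. A reader might infer that the authors chose to disregard the stratification; the text does not support that. What remains is that the article does state a model: the regression type, what is adjusted for, and how. In the same section it lists covariates for another analysis. The stated model does not reflect the stated randomisation, so it is reasonable to ask that it be completed or that the terms be confirmed as already prespecified.

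Second, nothing stated is invalid. The LAZ comparison without strata is unbiased by randomisation, the sample size was set without covariates, and any miscalibration is in the conservative direction. All of this stands. A reader might infer a raised false-positive rate, and the calculation shows the opposite.

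Third, the loss cannot be sized from the document. This also stands: every gain above depends on an assumed share of variance, and a share of zero gives no gain. A statement that precision is definitely being lost, or lost by a known amount, goes beyond what the article supports.

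Fourth, adjusting for maternal height is a choice, and a trial may legitimately do without it. That is right, so it is offered only as a secondary improvement.

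**Conclusion.** The point holds in a limited form. The final model as stated carries a random cluster effect and no term for the strata used to randomise. If the strata predict LAZ, its standard errors are too large and its test conservative. With 120 clusters of 21, ICC 0.035, and strata explaining an assumed 10-30% of between-cluster variance, true alpha is about 0.045-0.036, and stratum terms would raise power from about 83-84% to 84-87%. If the strata explain nothing, the stated model is correctly sized and nothing is gained. The LAZ estimate is unbiased in every case.

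This is a nearly free improvement that brings the analysis into line with the design. It is not an error that threatens the trial's conclusion. Maternal height would add about 2 points of power if it explains 8% of within-cluster variance, which is likewise an assumption.

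**What to change.** State the primary LAZ model as arm plus the randomisation strata as fixed effects, with a random cluster intercept, and use the same stratum terms in the logistic models. The strata can enter as district and hamlet group (1 + 2 = 3 degrees of freedom) or as all six strata as randomised (5 degrees of freedom). Either is small against 120 clusters. If an existing analysis plan already does this, a sentence confirming it is enough.

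As an optional second step, prespecify maternal height as a covariate and also report the model with strata only, so that readers can see what the covariate changes. Do not adjust for third-trimester MUAC or birth size. The intervention aims at maternal nutrition in pregnancy and may affect both, so adjusting for them could remove part of its effect.

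The cost is a line or two in the analysis plan, written before the arms are unblinded. No new data are needed: the strata are known for every cluster, and maternal height is part of the enrolment visit.
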